### Outcome assessment

Participants will be assessed at baseline and the four, 12, and 24 week follow-up sessions by an assessor blinded to group allocation. The physiotherapists, participants and investigators will be asked to avoid giving information which may reveal group allocation to the blinded assessor. Assessor blinding will be checked after each follow-up assessment. The assessor will be asked if he/she was unblinded and will guess the allocation of each participant.

Demographic information will be collected and an X-ray assessment will be carried out by the blinded assessor at the baseline assessment. The X-ray assessment will determine the angle at which the fractured ankle was immobilised and the number of malleoli involved, in order to investigate the relationships between the angle of immobilisation and fracture severity with outcome.

The primary outcomes will be activity limitation and quality of life. They will be measured by the Lower Extremity Functional Scale [42] and the Assessment of Quality of Life scale [43], respectively. On the Lower Extremity Functional Scale, participants will rate the difficulty they have in performing 20 activities on a five-point scale from zero (extreme difficulty or unable to perform activity) to four (no difficulty). The maximum score is 80 points and a higher score denotes less limitation in activity. When tested in a sample of participants with lower limb injuries that included ankle fracture, the scale showed high internal consistency (alpha = 0.96) and test-retest reliability (intraclass correlation coefficient = 0.86), and correlated well with the physical component of the Short Form 36 [42]. The Lower Extremity Functional Scale is capable of discriminating between patients requiring walking aides and patients not requiring walking aides, and has moderate correlations with weight-bearing status and ankle movement [44].

The Assessment of Quality of Life is designed to measure health-related quality of life, and has 15 questions covering five dimensions: illness, independent living, social relationships, physical senses and psychological wellbeing [43]. It has high internal consistency (alpha = 0.81) [43]. The Assessment of Quality of Life is sensitive to changes in health states and is highly correlated with other commonly-used quality of life scales [46]. Population norms have been calculated for the Australian population [46].

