Ankle dorsiflexion range of motion will be measured using the weight-bearing lunge method [52]. Participants will stand with the affected foot on the ground and the great toe against the wall, and will bend the knee to touch the wall. If the knee cannot reach the wall, the minimum distance between the knee and the wall without the heel lifting will be recorded in millimetres as a negative value. If the knee can touch the wall, the foot will be gradually moved back and the maximum distance between the great toe and the wall without the heel lifting will be recorded in millimetres as a positive value. Measured this way, ankle dorsiflexion at the time of cast removal has been shown to be a significant predictor of disability, perceived change in symptoms and active ankle dorsiflexion range six weeks and six months after ankle fracture [14]. The weight bearing lunge method has high inter-rater and intra-rater reliability (intraclass correlation coefficient 0.99 and 0.97 to 0.98 respectively) in the healthy population [52].

Pain on standing with equal weight distribution and during stair descent will be measured using a 100-mm visual analogue scale, labelled "no pain" on one end and "worst pain ever" on the other. The pain visual analogue scale correlates positively with other self-reported measures of pain intensity [53,54]. It has high test-retest reliability (intraclass correlation coefficient = 0.71 to 0.99) [53], and is highly responsive in detecting change [54]. Participants will also rate their return to usual work, and return to usual sport and leisure activities using a 100-mm visual analogue scale, marked "not participating at all" at one end and "return to full level" at the other.

Global perceived effect of treatment will be measured on an 11-point scale, where participants rate their change in symptoms from -5 (vastly worse) to +5 (completely recovered). A scale of this kind is the most frequently used external criterion to which score changes on other outcome measurements are compared [42,55-57]. However its use as an external criterion is under debate [58,59], and there is little information regarding its validity and reliability [59].

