Satisfaction with physiotherapy treatment will be measured at the four-week follow-up assessment on a 100-mm visual analogue scale marked "completely unsatisfactory" at one end and "best possible" at the other. At all follow-up assessments, participants will be asked if the physiotherapy treatment has had any negative effects and, if so, the nature of the effects. They will also record whether they have had treatment other than physiotherapy for the fractured ankle.

The treating physiotherapist will complete a survey for every participant at each follow-up assessment until discharge. Information gathered on this survey will be: the date and reason of discharge (if applicable), number of physiotherapy sessions scheduled, number of physiotherapy sessions attended, exercises prescribed and repetitions completed, any other physiotherapy treatment administered, and, for the treatment group only, the dates, number of sets and duration of the joint mobilisation treatment. This information will be analysed to obtain the length of physiotherapy required, percentage of scheduled sessions attended, compliance of participants to the exercise programme, and compliance of physiotherapists to the experimental protocol.

Data will be collected on paper forms and manually entered into a computer programme. Several strategies will be implemented to ensure the accuracy of the data. Data collection forms will be checked for completion. Data entry will be performed twice and the two entries will be compared to check for errors. Range checks will be performed on outcome values at the completion of data entry.

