### Statistical analysis

Data analysis will be undertaken at the completion of data acquisition and will be by intention to treat (that is, participants will be analysed according to group allocation regardless of compliance) [60]. Missing data will be replaced by the last known value carried forward. The statistician will be given coded data to ensure blinding.

Separate analyses will be performed on the four, 12 and 24 week data, with the four-week (i.e., the end of the intervention period) follow-up being the primary time point for analysis. To test the effects of treatment, between-group differences will be examined with analysis of covariance using a regression approach. The emphasis will be on estimation, but hypothesis tests will also be conducted (alpha = 0.05). Pre-test scores will be entered into the model as the only covariate.

In a secondary analysis designed to test the influence of fracture severity on treatment effects, additional terms (fracture severity, group by fracture severity interaction) will be entered into the regression model. Fracture severity will be categorised into two levels based on the number of malleoli involved: less severe (unimalleolar fractures) and more severe (bimalleolar or trimalleolar fractures). The effect of fracture severity on treatment will be determined by examining the interactions between group of allocation and fracture severity.

Ninety participants (45 per group) will participate in the trial. This sample size provides a 90% probability of detecting a difference between group means of 10 points on the Lower Extremity Functional Scale, assuming a standard deviation of 12 based on a recently published study [41]. These calculations assume a correlation of 0.6 between pre- and post-test measures and an alpha of 0.05, and allowed for 10% dropouts and 20% non-compliance.

The economic evaluation will consist of cost-effectiveness and cost-utility analyses. The cost-effectiveness analysis will use the Lower Extremity Functional Scale as a measure of effectiveness. The cost-utility analysis will use the Assessment of Quality of Life as a measure of utility [43]. The analyses will examine differences between treatment and control participants in terms of costs incurred and reductions in perceived disability (cost-effectiveness analysis) or utility gained (cost-utility analysis).

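### Global perceived effect has no pre-test score, so the sole-covariate rule leaves it unadjusted although the protocol names a predictor that the trial appears to measure at baseline; the loss is precision only

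*Protocol article*

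**What the plan says.** The Statistical analysis section of the protocol article gives one approach to treatment effects: "between-group differences will be examined with analysis of covariance using a regression approach", carried out separately at four, 12 and 24 weeks. The covariate rule is "Pre-test scores will be entered into the model as the only covariate". No exception is named for outcomes that lack a pre-test score. The only further model terms are fracture severity and its interaction with group, and these belong to a separate secondary analysis.

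The Outcome assessment section defines global perceived effect as a scale on which "participants rate their change in symptoms from -5 (vastly worse) to +5 (completely recovered". The same section describes the dorsiflexion measure ("Ankle dorsiflexion range of motion will be measured using the weight-bearing lunge method") and says that dorsiflexion measured this way at cast removal is "a significant predictor of disability, perceived change in symptoms and active ankle dorsiflexion range six weeks and six months after ankle fracture". On timing it says "Participants will be assessed at baseline and the four, 12, and 24 week follow-up sessions". Under Participants, entry requires that the cast came off within the previous seven days.

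Two other secondary outcomes also have no pre-test score. One is satisfaction ("Satisfaction with physiotherapy treatment will be measured at the four-week follow-up assessment on a 100-mm visual analogue scale"). The other is the number of days from cast removal to pain-free walking.

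**The concern.** The covariate rule suits outcomes measured both before and after treatment. It does not suit a rating of change, which has no value before treatment begins. For global perceived effect the rule therefore supplies no covariate, and the word 'only' discourages adding one. The protocol itself identifies a baseline variable that predicts perceived change and appears to collect it, so a source of precision is set aside without a stated reason.

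What is at stake is the width of the confidence interval for one secondary outcome. That has some weight because the Statistical analysis section says it will emphasise estimation over testing. The choice is also best made in advance: a covariate added after baseline imbalance has been seen would look data-driven and would depart from the stated rule.

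**Working it through.** **The plan's own figure.** The protocol gives no precision or power figure for global perceived effect. Its sample size of 45 per group concerns the Lower Extremity Functional Scale: difference 10, SD 12, correlation 0.6, power 90%, alpha 0.05 (taken as two-sided), 10% dropout and 20% non-compliance. With a change-score SD of 12 × √(2 × (1 − 0.6)) = 10.73, the requirement is 25 per group. Dividing by 0.9 × 0.8² = 0.576 gives 43.4, or 44 per group, close to the stated 45. This does not bear on the present point, which uses only the 45 per group.

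**Does the rule reach the outcome?**
1. The covariate is the pre-test score and nothing else (Statistical analysis).
2. Global perceived effect rates change, so no pre-test score exists (Outcome assessment).
3. The regression therefore contains group alone, which is an ordinary difference in means.
4. Dorsiflexion by the weight-bearing lunge is a trial outcome. Participants are assessed at baseline, within about a week of cast removal, so the named predictor should be available. Table 1 is not shown, so this rests on the text.

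**What adjustment would gain.** Let r be the correlation, within groups, between baseline dorsiflexion and global perceived effect. The protocol gives no value, so r is assumed over a range.

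- Residual variance ratio: 1 − r²
- Reduction in standard error: 1 − √(1 − r²)
- Power after adjustment, where unadjusted power is 80%: Φ((1.960 + 0.842)/√(1 − r²) − 1.960)

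| Assumed r | Variance ratio | Reduction in standard error | Power, from 80% |
|---|---|---|---|
| 0.1 | 0.99 | 0.5% | 80.4% |
| 0.2 | 0.96 | 2.0% | 81.6% |
| 0.3 | 0.91 | 4.6% | 83.6% |
| 0.4 | 0.84 | 8.3% | 86.4% |
| 0.5 | 0.75 | 13.4% | 89.9% |

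For example, at r = 0.4, √0.84 = 0.917 and 1 − 0.917 = 8.3%.

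**Is the unadjusted comparison sound?** A simulation of 20,000 trials with 45 per group and no treatment effect, outcome variance 1, gave the following.

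| r | Analysis | Type I error | Mean estimate | SD of estimate |
|---|---|---|---|---|
| 0.2 | Unadjusted | 0.0492 | 0.0007 | 0.2110 |
| 0.2 | Adjusted | 0.0498 | 0.0011 | 0.2080 |
| 0.4 | Unadjusted | 0.0505 | −0.0003 | 0.2107 |
| 0.4 | Adjusted | 0.0492 | −0.0005 | 0.1944 |

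Both analyses hold the 5% level and show no bias. The simulated gains are 1 − 0.2080/0.2110 = 1.4% and 1 − 0.1944/0.2107 = 7.7%. These are slightly below the formula's 2.0% and 8.3% because the slope has to be estimated. If a similar shortfall of about 0.6 percentage points applies at r = 0.1, the 0.5% there is effectively nil.

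**The case against.** The strongest reply is that nothing here is wrong. Without a pre-test score the model reduces to a difference in means, which is valid. A uniform rule of pre-test score or nothing is simple and defensible. The covariate sentence can also be read as applying only to outcomes that have a pre-test score. The outcome is secondary, and the protocol itself says that little is known about the scale's validity and reliability. A condensed article may leave such detail to a fuller plan.

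Most of this stands, and it is why the point is minor. The reply on omitted detail does not fully answer it: the article is not silent but fixes a restrictive rule, and a later plan that added a covariate for this outcome would sit awkwardly with that wording.

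The evidence for the predictor is also imperfect. It is reported for six weeks and six months after fracture, whereas the trial's times run from randomisation and its primary time point is four weeks. Being a significant predictor does not imply a correlation of 0.3 or more.

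Four stronger readings are tempting, and the document does not support them.
- A reader might infer that the analysis cannot be carried out. It can, as a model with group alone.
- A reader might infer that chance imbalance in dorsiflexion makes the result invalid. Across randomisations the unadjusted interval already allows for such imbalance.
- A reader might infer a firm saving in participants. That depends wholly on a correlation the document does not give.
- A reader might infer that satisfaction should be adjusted for the baseline Lower Extremity Functional Scale. Nothing in the protocol says that this scale predicts satisfaction.

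**Conclusion.** The point holds at low severity, as an inexpensive gain in precision and not as the correction of an error. The covariate rule leaves global perceived effect unadjusted although the protocol names a relevant predictor. The comparison remains unbiased with the correct type I error.

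The size is uncertain: the reduction in standard error runs from 0.5% to 13.4% across the assumed correlations and is negligible at the lower end. This rests on three assumptions: dorsiflexion is recorded at baseline for all participants, its relation to perceived change is roughly linear, and the reported prediction carries over to the trial's own time points. The last is least certain at four weeks. The primary outcomes are unaffected.

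**What to change.** Amend the covariate sentence in the Statistical analysis section, before any unblinded data are seen, along these lines: *Where an outcome has a pre-test score, that score will be the only covariate. For global perceived effect, baseline weight-bearing lunge dorsiflexion will be the only covariate. Satisfaction with treatment and days to pain-free walking have no pre-test score and will be compared without a pre-test covariate.*

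Naming the last two outcomes completes the rule. The cost is one sentence and one residual degree of freedom for global perceived effect (90 − 3 = 87 instead of 90 − 2 = 88 with complete data). If baseline dorsiflexion is recorded as the text indicates, no new data are needed.

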The treatment cost of ankle fracture has been estimated in studies from Britain and Canada [37,38], but to-date there are no randomised controlled trials. In a retrospective audit, costs of hospitalisation were significantly greater in those who were operated on within 24 hours, compared to those who were operated on more than 24 hours after presentation [37]. The average extra cost per patient was £990 (1998 British pounds). A prospective pilot study reported that the total hospitalisation and outpatient medical costs were $2,134 (United States dollars) per patient over a 12-month period [38]. But this study did not include a control group, and hence no comparisons of costs or quality of life measures. Neither of these studies assessed utilisation of services or included the cost of outpatient physiotherapy. Only one published study has reported an economic analysis of joint mobilisation [39], but the comparisons made were between high-grade and low-grade mobilisation for the shoulder. Therefore, despite the common use of joint mobilisation as a treatment technique, its current use after ankle fracture is based on clinical experience and limited evidence of effectiveness and cost-effectiveness.

The primary aim of this trial is to determine whether adding joint mobilisation to an exercise programme is more effective and cost-effective than exercise alone after cast immobilisation for ankle fracture in adults. A secondary aim is to determine if treatment effects are influenced by fracture severity.

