The incremental cost-effectiveness (utility) ratio (ICER) will be calculated as: ICER = (C_E _- C_C_)/(U_E _- U_C_), where C is average cost, U is the average effectiveness or utility score, and subscripts E and C denote the treatment and control arms. Joint mobilisation can be said to be cost-effective relative to exercise alone if it produces less perceived disability and/or greater utility at a lower cost, or the cost per disability avoided or per quality of life gained (i.e., the ICER) is less than some threshold value (e.g., $50,000 in Australian dollars). Sensitivity analysis will be undertaken to explore the robustness and validity of the results. That is, both costs and outcomes will be varied in line with results from similar studies reported in the literature and the upper and lower bounds of the results from this trial.

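### The ICER denominator is defined as a difference in average scores with no baseline adjustment named, and does not match the ANCOVA planned for the same outcomes

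*Protocol article*

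**What the plan says.** Cost-effectiveness is part of the primary aim. The Background asks whether adding joint mobilisation is "more effective and cost-effective than exercise alone after cast immobilisation for ankle fracture in adults".

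For effectiveness, the Statistical analysis section says that "between-group differences will be examined with analysis of covariance using a regression approach", and "Pre-test scores will be entered into the model as the only covariate". The covariate will be available: "Participants will be assessed at baseline and the four, 12, and 24 week follow-up sessions by an assessor blinded to group allocation" (Outcome assessment).

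The economic evaluation uses the two primary outcomes again. "The cost-effectiveness analysis will use the Lower Extremity Functional Scale as a measure of effectiveness", and "The cost-utility analysis will use the Assessment of Quality of Life as a measure of utility". The arms are to be compared "in terms of costs incurred and reductions in perceived disability (cost-effectiveness analysis) or utility gained (cost-utility analysis").

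The incremental cost-effectiveness ratio (ICER) is then written as (C_E - C_C)/(U_E - U_C), "where C is average cost, U is the average effectiveness or utility score". No baseline term, adjusted mean or time point is given for U. The sensitivity analysis varies costs and outcomes by literature values and by the bounds of the trial's own results. It does not name a baseline-adjusted ICER.

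**The concern.** The plan adjusts LEFS and AQoL for baseline when it judges effectiveness. It then writes the cost-effectiveness denominator for the same scores in a form that, read plainly, is a difference of arm averages. The wording about reductions and gains permits a second reading, a difference in change from baseline. Only a third reading, an adjusted difference, agrees with the planned ANCOVA, and no sentence states it.

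Allocation is stratified by site only (Design), so nothing in the design balances baseline LEFS or AQoL in 90 participants. Whatever imbalance occurs would pass in part into the denominator under either of the first two readings. Because the denominator divides, a moderate shift changes the ratio by a larger proportion when the true effect is small. The report could also carry two different treatment effects on one outcome, one for effectiveness and one inside the ICER.

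**Working it through.** **Inputs (Statistical analysis):** 45 per arm; LEFS SD 12; pre-post correlation r = 0.6; design effect 10 points; alpha 0.05; power 90%; allowances of 10% dropout and 20% non-compliance. **Assumptions:** SD equal at baseline and follow-up, so the regression slope on baseline equals r; two-sided test.

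**The plan's own figure.** Using follow-up scores, n per arm = 2 × [12 × (1.960 + 1.282)/10]² = 30.3, so 31; 31/(1 - 0.3) = 44.3, so 45 per arm and 90 in total. Using change scores, 30.3 × 2(1 - 0.6) = 24.2, so 25; 25/(0.8² × 0.9) = 43.4, so 44 per arm and 88 in total. The stated 90 is therefore reproduced or closely approached under common conventions, and this point does not challenge it.

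**Standard error of the LEFS denominator, 45 per arm.**

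- Follow-up means: 12 × √(2/45) = 2.53 (variance 6.40)
- Change scores: 2.53 × √[2(1 - 0.6)] = 2.26 (variance 5.12)
- ANCOVA: 2.53 × √(1 - 0.6²) = 2.02 (variance 4.10)

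ANCOVA variance is lower by 1 - 4.10/6.40 = 36% against follow-up means, and by 1 - 4.10/5.12 = 20% against change scores.

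**Chance imbalance carried into the denominator.** The baseline difference between arms has SE 12 × √(2/45) = 2.53 points.

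- Follow-up means carry r × imbalance: SD 0.6 × 2.53 = 1.52, 95% range ±2.98
- Change scores carry -(1 - r) × imbalance: SD 0.4 × 2.53 = 1.01, 95% range ±1.98, in the opposite direction
- ANCOVA removes this component

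The pieces add up: 4.10 + 1.52² = 6.40 and 4.10 + 1.01² = 5.12, to rounding.

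**Effect on cost per LEFS point of a one-SD baseline imbalance (2.53 points), cost difference held fixed.**

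| True effect | Follow-up means | Change scores |
|---|---|---|
| 10 points | 10/8.48 = 1.18 or 10/11.52 = 0.87 | 10/8.99 = 1.11 or 10/11.01 = 0.91 |
| 5 points (illustrative) | 5/3.48 = 1.44 or 5/6.52 = 0.77 | 5/3.99 = 1.25 or 5/6.01 = 0.83 |

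**Dependence on r.** The ICER names no time point, so the relevant correlation may not be 0.6. The variance saving is r² against follow-up means and (1 - r)/2 against change scores. At an assumed r = 0.3 these are 9% and 35%. ANCOVA does no worse than either alternative at any r; which alternative is the poorer depends on r.

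**AQoL.** The documents give no SD or correlation. Purely as an assumption, SD 0.15 to 0.30 with r 0.3 to 0.7 gives a 95% range carried into a difference of follow-up means of 1.96 × r × SD × √(2/45), about ±0.02 to ±0.09 utility units.

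**The case against.** The strongest reply is that the formula is generic. It says what is divided by what, not how the incremental effect is estimated, and an average can be an adjusted average. The ANCOVA is stated for treatment effects in general, and LEFS and AQoL are the primary outcomes under it. A condensed article may leave the estimator to a fuller plan. Part of this stands: a reader might infer that the plan commits to a raw denominator, but the text never uses such a word and does not exclude adjusted means. What remains is that the article does write out the estimator and defines its symbols. Neither the plain reading nor the change-score reading gives the planned adjusted effect, and nothing extends the ANCOVA to the ICER.

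Second, a reader might infer bias. Allocation is random and concealed, so the unadjusted difference is unbiased in expectation. Stratifying by site alone is not an error. This objection stands in full, and the issue is confined to precision and to the imbalance that happens to occur.

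Third, the planned sensitivity analysis uses the trial's own upper and lower bounds. If these are 95% limits of a difference in follow-up means, they span 1.96 × 2.53, about ±5 LEFS points, which is wider than the ±2.98 carried by imbalance. That would show the uncertainty, but it leaves the central estimate uncorrected and does not recover the lost precision.

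Fourth, a reader might infer that imbalance would push the ICER across the example threshold, or that the trial loses power to show a non-zero denominator. Neither is supported. The documents give no expected costs, and no test of the denominator is planned.

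**Conclusion.** The point holds as a mismatch between two parts of the Statistical analysis section. The ICER denominator is defined by arm averages with no adjustment named, and the surrounding wording also allows change scores. The planned effect estimate for the same outcomes is an ANCOVA on the pre-test score.

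For LEFS, at SD 12 (equal at both times), r = 0.6 and 45 per arm, following the formula would mean a denominator variance 56% larger than ANCOVA's (6.40/4.10) with follow-up means, or 25% larger (5.12/4.10) with change scores. A one-SD baseline imbalance would move cost per LEFS point by roughly -13% to +18%, or -9% to +11%, at the 10-point design effect. These figures depend on the correlation at the time point eventually used. The size for AQoL, and any consequence for the threshold decision, cannot be established from the document. The point concerns precision and consistency in an analysis that serves the primary aim. It shows neither bias nor a wrong conclusion.

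**What to change.** After the ICER formula in the Statistical analysis section, state that U_E - U_C is the baseline-adjusted between-group difference, that is, the group coefficient from the regression already specified there. The covariate is the pre-test LEFS score for the cost-effectiveness analysis and baseline AQoL utility for the cost-utility analysis. Report the ICER based on the unadjusted difference as a sensitivity analysis. Align the wording about reductions and gains with this definition, so that it is not taken to mean change scores.

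This takes one or two sentences. The baseline scores are already collected and the regression is already planned, so no participants, visits or staff are added.

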### Economic analysis

The economic analysis will be conducted from the perspective of the Australian healthcare system and the individual patient, with data collected in a survey every four weeks from the end of the four-week intervention period to the 24-week follow-up assessment. Participants will record all out-of-pocket expenses incurred due to the fractured ankle, including the frequency and costs associated with physiotherapy, other health and hospital services, and the costs of medication. Figure 4 indicates the type of resources which will be captured, the sources of data, and proposed methods of valuation. At the four-week follow-up assessment, participants will also be asked to provide socio-demographic information such as their usual main activity, normal annual household income, the type of private health insurance they have (if any), and whether they are renting, boarding or owners of their homes.

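### The cost-effectiveness ratio divides costs surveyed to week 24 by a score difference with no time dimension, and sets one unit-less $50,000 example against both LEFS and utility, so it cannot support a threshold verdict

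*Protocol article*

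**What the plan says.** All of this is in the protocol article.

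- **Ratio (Statistical analysis).** The ICER is (C_E − C_C)/(U_E − U_C), "where C is average cost, U is the average effectiveness or utility score".
- **What U is (Statistical analysis).** For the first analysis the text reads "The cost-effectiveness analysis will use the Lower Extremity Functional Scale as a measure of effectiveness". For the second, U comes from a different instrument: "The cost-utility analysis will use the Assessment of Quality of Life as a measure of utility".
- **Decision rule (Statistical analysis).** There are two routes to calling mobilisation cost-effective. The first is dominance: "if it produces less perceived disability and/or greater utility at a lower cost". The second is a threshold test on "the cost per disability avoided or per quality of life gained (i.e., the ICER"). That test is passed when the ratio in question "is less than some threshold value (e.g., $50,000 in Australian dollars").
- **Cost data (Economic analysis).** Surveys are made every four weeks "from the end of the four-week intervention period to the 24-week follow-up assessment".
- **LEFS scale (Outcome assessment).** "The maximum score is 80 points and a higher score denotes less limitation in activity".

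Outcomes are assessed at baseline and at weeks 4, 12 and 24. Week 4 is the primary time point for the effectiveness analysis. The article names no time point for U, states no window for C in the formula, and does not mention QALYs.

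**The concern.** Costs accumulate over time, whereas a difference in average utility score is a level. Dividing one by the other gives dollars per unit of score, and the result does not depend on whether the gain lasts one week or twenty. The article makes a fading effect plausible: its Background says the analgesic effect of peripheral joint mobilisation may be short lasting, and mobilisation stops at week 4.

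The threshold has a separate problem. One ratio is per point on an 80-point scale and the other is per unit of utility. A single sum of money cannot be the limit for both. The two are joined by *or*, so passing on the LEFS ratio alone could be read as enough.

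Cost-effectiveness is part of the stated primary aim, and this paragraph is its decision rule. If mobilisation turns out both better and dearer, the answer would depend on the unit and visit chosen as much as on the data.

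**Working it through.** The article states no cost difference, utility difference or ICER, so there is no economic figure to reproduce. The check compares the ratio as defined with a cost per QALY.

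**Inputs from the article:** visits at weeks 0, 4, 12 and 24; example threshold AUD 50,000; LEFS design difference of 10 points.

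**Assumptions (not in the article):** AQoL is scored as a utility on which QALYs are defined; the between-group difference is zero at baseline; the differences d4, d12 and d24 at the later visits are as in the table; a year has 52 weeks.

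**Formulas**

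- QALY gain (trapezoids) = [4·(0 + d4)/2 + 8·(d4 + d12)/2 + 12·(d12 + d24)/2]/52 = (6·d4 + 10·d12 + 6·d24)/52.
- Factor = cost per QALY ÷ score ratio = score difference ÷ QALY gain. The extra cost cancels.
- Largest extra cost that passes = $50,000 × score difference (as written) or $50,000 × QALY gain.

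**Example, constant 0.05:** (0.30 + 0.50 + 0.30)/52 = 1.10/52 = 0.0212 QALY. Factor = 0.05/0.02115 = 2.36. Limits: $50,000 × 0.05 = $2,500 and $50,000 × 0.02115 = $1,058.

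| d4 / d12 / d24 | QALY gain | Visit used for U | Factor | Passes as written up to | Passes per QALY up to |
|---|---|---|---|---|---|
| 0.05 / 0.05 / 0.05 | 0.0212 | any | 2.4 | $2,500 | $1,058 |
| 0.05 / 0.025 / 0 | 0.0106 | week 4 | 4.7 | $2,500 | $529 |
| 0.05 / 0 / 0 | 0.0058 | week 4 | 8.7 | $2,500 | $288 |
| 0.02 / 0.03 / 0.05 | 0.0138 | week 24 | 3.6 | $2,500 | $692 |
| 0.02 / 0.03 / 0.05 | 0.0138 | week 4 | 1.4 | $1,000 | $692 |
| 0.01 / 0.05 / 0.05 | 0.0165 | week 4 | 0.6 | $500 | $827 |

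The verdict at $50,000 differs only when the extra cost lies between the last two columns. In the final row the error runs the other way: the score ratio is too strict. In the second and third rows, taking U at week 24 gives a score difference of zero and no ratio at all, although QALYs were gained.

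**LEFS:** at $50,000 per point, a 1-point gain passes at any extra cost up to $50,000, and the 10-point design difference up to 10 × $50,000 = $500,000 per patient. For scale, the scheduled difference between arms in the intervention period is three sessions (2 × 4 = 8 against 2 + 3 = 5).

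**The case against.** The strongest reply has three parts.

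1. *This is an article, and the accumulation of utilities, the cost window and baseline adjustment usually sit in a fuller plan.* Silence on those details would indeed be no finding. But the article prints the formula and defines U as an average score. Followed as printed, that gives the wrong unit.
2. *The $50,000 is only an example of some threshold, and no text commits to $50,000 per LEFS point.* This stands. The $500,000 figure shows what would follow if the example were applied to that ratio; it is not a rule the article fixes. What remains is that one figure, with no unit of effect, is set against both ratios.
3. *A sensitivity analysis is planned.* It varies the values of costs and outcomes, not the unit of the denominator, so it does not cure the mismatch.

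A reader might also infer that the distortion is always at least twofold. It is not: with a week-4 score the factor is 1.4 or 0.6 for the late-emerging gains in the table. Nor should the $500,000 be set against the $2,134 per patient in the Background. That is a United States dollar total for hospital and outpatient medical care, from a study that excluded outpatient physiotherapy, whereas the $500,000 is an increment in Australian dollars.

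**Conclusion.** Wrong as written. The ratio and its single example threshold cannot support a cost-effectiveness verdict when mobilisation is both dearer and better.

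For an assumed gain of 0.05 with no baseline difference, the score ratio understates cost per QALY about 2.4 times if the gain holds from week 4 to week 24, and about 8.7 times if it is present at week 4 only and U is taken there. For late-emerging gains with a week-4 score the factor falls to 1.4 or below 1. The $50,000 example does not discriminate on LEFS points.

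A reader might go further and conclude that the trial's verdict will be wrong. The document does not support that. Dominance uses neither the ratio nor the threshold, and in the constant case only extra costs between about $1,058 and $2,500 change sides. Three things remain assumptions: the utility differences and their time course; the 24-week window for C, inferred from the survey schedule; and the reading of $50,000 as a per-QALY figure, which the article never states.

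**What to change.** Change the economic paragraphs of the Statistical analysis section as follows.

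- Define the cost-utility denominator as QALYs: the area under the AQoL utility curve over weeks 0, 4, 12 and 24, with the between-group difference adjusted for baseline utility.
- State that C covers the same 24 weeks.
- Apply the $50,000 threshold only to cost per QALY, and label it so.
- Report cost per LEFS point with its interval and a stated time point, and without a threshold.

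The cost is analysis wording only, since assessments already take place at all four times; no design, sample size or data collection changes. The price for the sponsor is that the cost per unit gained will usually look less favourable than under the score ratio.
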